### Randomization

After the assessment of the sample calculation, the study will aim towards including a total of 122 patients in which the first 56 patients will be examined with radiostereometric analysis and DXA. The patients are divided into two, equally sized and equally randomized to both arms, groups:DELTA Xtend Reverse Shoulder System Lateralized Glenosphere Line Extension (intervention group)Standard DELTA Xtend Reverse Shoulder System (control group).

In the operation room, the randomization is done on the trial laptop, short after the perioperative evaluation of the quality of bone stock. Thereby, the randomization is done when the patient is anaesthetized.

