**Methods:**

In this randomized controlled trial, all Danish citizens with rotator cuff arthropathy or degeneration of the glenohumeral joint with severe posterior wear and allocated for a reverse total shoulder arthroplasty at the department of orthopaedic surgery at Herlev and Gentofte Hospital, Copenhagen University Hospital, will be considered for participation. The exclusion criteria are as follows: below 50 years of age, cognitive or linguistic impairment, insufficient glenoid bone stock, previous fracture in the upper extremity and autoimmune-mediated inflammatory arthritis. There will be included a total of 122 patients of which 56 will participate in the radiostereometric analysis. This number of patients allows 20% to drop out. The co-primary outcomes are the pattern and magnitude of the migration of the glenoid component assessed by radiostereometric analysis and the Western Ontario Osteoarthritis of the Shoulder index. The secondary outcomes are inferior scapular notching, patient-reported and functional outcomes (Oxford shoulder score, Constant-Murley score and pain), side effects and complications, changes in bone mineral density and economy. The included patients will be examined before the surgery, within 1 week and 3, 6, 12 and 24 months after.

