### Sequence generation and allocation

The randomization done on the trial laptop is done in the Research Electronic Data Capture (REdCap), in which the computer generates the randomization sequence by block randomization, stratified for gender and age and equally randomized to both shoulders (1:1 allocation). The primary investigator reads the allocation from the trial laptop to inform the surgeon. An independent statistician prepares the randomization table before the study is initiated.

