### Surgical procedure

The procedures will be performed at Herlev and Gentofte Hospital, Copenhagen University Hospital. This unit performs around 300 primary and revision shoulder arthroplasties each year. From the evaluation of the number of surgeries from 2015 to 2016, it is expected to perform surgery on 75 patients with reverse shoulder arthroplasty for rotator cuff arthropathy every year. To minimize a potential learning curve and ensure a high surgical standard, the study is performed as a single-centre study and six experienced shoulder surgeons will be performing this type of surgery regularly using the same implant. To determine the potential learning curve applied by the lateralization devices, there will be done subgroup analyses at the end of the study, to compare the first and second half of the patients. Prior to the initiation of the study, each of the six surgeons shall have performed a minimum of 3 surgeries with the DELTA Xtend Reverse Shoulder System Lateralized Glenosphere Line Extension to minimize a potential learning curve problem.

The patient is under general anaesthesia and in a beach chair position during the procedure. Surgical technique, including soft tissue balancing and exposure instrumentation, is standardized for all patients. All surgeries are done with the standard deltopectoral approach and subscapularis tenodesis. All patients are treated with either (1) DELTA Xtend Reverse Shoulder System Lateralized Glenosphere Line Extension or (2) the standard DELTA Xtend Reverse Shoulder System according to the guidelines from the manufacturer. Perioperatively, approximately 20 tantalum markers (0.8 mm, Tilly Medical Products, Lund, Sweden) are placed in the bone at the proximal humerus and the glenoid around the components; we aim for the widest non-linear distribution, which will allow us to measure segmental motion with Mb-RSA software (Model-based RSA 4.1, 2003-2014 RSAcore Department of orthopedics Leiden University Medical Centre) using computer-aided design (CAD) models.

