Size 1 and 2 humeral components will be used, in which all patients are treated with a cemented humeral monobloc component. Based on the medialization measured by plain radiographs, there will be used a 4-mm or 8-mm lateralized glenosphere if randomized for the intervention group. If randomized for the control group, a standard glenosphere is used. Prophylactic cloxacillin 2 g and benzylpenicillin 1.2 g are given preoperatively and at 6 and 12 h. If a patient cannot tolerate the standard prophylactic treatment, cefuroxime 1.5 g is given preoperative and at 6 and 12 h.

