### Protocol violations, revision and drop-out

If the surgeon during the surgery regards it as impossible to insert a glenoid component, the surgery can be converted to a stemmed hemiarthroplasty using the DELTA Xtend humeral stem and a CTA head.

If patients drop out of the trial, it will be recorded along with the reason for drop-out. The patient in question will be included in the final mixed-effect model analysis, except for patients who drop out before 3 months, who cannot be included in the analysis. At the end of the study, a sensitivity analysis will be performed to evaluate the impact of missing data on the overall results of the trial. It will be recorded if there are indications that some patients do not comply with rehabilitation.

In case of revision surgery, reason and new arthroplasty type will be recorded. Additionally, the patient will prior to revision surgery be assessed by DXA, radiostereometric analysis, patient-reported outcome and clinical outcome if possible. The patient will stay included in the study and the 2-year analysis with the latest follow-up.

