## Discussion

This study aims to determine if DELTA Xtend Reverse Shoulder System Lateralized Glenosphere Line Extension has a better outcome than the Standard DELTA Xtend Reverse Shoulder System. The patients will be divided into two groups and equally randomized and treated. There is a possibility of being treated with what turns out to be an inferior arthroplasty. Today, it is not known if one treatment is better than the other as the two types of glenospheres are considered equal effective and safe.

Sirveaux et al. [4] reported that inferior scapular notching was associated with increased risk of revision, and Mollon et al. [5] described lower clinical outcomes for these patients. This study aims to explore metallic lateralization as a solution to prevent inferior scapular notching and subsequently better outcomes. Lateralization of the glenoid off-set has earlier been reported as the most efficient technique to avoid inferior scapular notching [8]. Furthermore, lateralization has been described to improve movement [9] but at the same time makes greater demands to the deltoid muscle [29]. There has also been reported a higher rate of loosening [8]. Implant migration can be the first sign of loosening. Radiostereometric analysis has been used to measure implant migration in numerous studies for more than 20 years [30], but this is, to our knowledge, the first time radiostereometric analysis is used to compare the outcome for conventional reverse shoulder arthroplasty and lateralized reverse shoulder arthroplasty in a randomized controlled trial. DXA has been used in shoulder patients before.

The model-based radiostereometric analysis technique is less precise than the marker-based method. However, precision error values are still acceptable for clinical studies aimed at evaluating implant migration [31]. The use of radiostereometric analysis for the evaluation of implant migration has been used frequently in the evaluation of hip and knee arthroplasty surgery. It has been shown that the late revision due to aseptic loosening of the tibial component in total knee arthroplasty is consistent with early radiostereometric analysis findings of continuous migration past the first postoperative year [32]. Therefore, it has been suggested that a small series of new arthroplasties should be monitored with radiostereometric analysis the first 2 years postoperatively, as part of a safe phased introduction of new arthroplasties [30, 33, 34].

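### Allocation is tied to the bone-stock check rather than to confirmed insertability or completed glenoid fixation, so conversions after randomisation and fixation with the arm known are not ruled out

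*Protocol article*

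**What the plan says.** All references are to the protocol article.

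- **Timing.** *Randomization*: the patient is anaesthetised and "the randomization is done on the trial laptop, short after the perioperative evaluation of the quality of bone stock". No later surgical step is named.
- **Who learns the arm.** *Sequence generation and allocation*: "The primary investigator reads the allocation from the trial laptop to inform the surgeon".
- **What differs between arms.** *Surgical procedure*: "there will be used a 4-mm or 8-mm lateralized glenosphere if randomized for the intervention group", with the size based on medialization on plain radiographs; "If randomized for the control group, a standard glenosphere is used". The *Discussion* likewise describes the comparison as one between two glenospheres: "it is not known if one treatment is better than the other as the two types of glenospheres are considered equal effective and safe".
- **Technique.** *Surgical procedure*: "Surgical technique, including soft tissue balancing and exposure instrumentation, is standardized for all patients". Tantalum markers are placed during surgery in the proximal humerus and in the glenoid around the components.
- **Eligibility.** The abstract and the exclusion list rule out "insufficient glenoid bone stock".
- **Failed insertion.** The section *Protocol violations, revision and drop-out* foresees this case: "If the surgeon during the surgery regards it as impossible to insert a glenoid component, the surgery can be converted to a stemmed hemiarthroplasty". The section does not say whether such a patient has already been randomised.
- **Outcome affected.** *Primary radiological outcome*: maximum total point motion (MTPM) of the glenoid component at 2 years, in the first 56 patients.

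**The concern.** When randomisation takes place during surgery, allocation is best revealed at the last moment before the arms diverge. Here they diverge at the glenosphere, but allocation is tied to an assessment of bone. The protocol's own provision for failed insertion shows that this assessment does not settle whether a glenoid component can be used.

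Two things follow if allocation is opened early.

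1. A randomised patient who is converted has no glenoid component, hence no MTPM and no reading for inferior scapular notching, yet still contributes a WOOS score after a different operation. The loss arises after allocation, through a decision by a surgeon who knows the arm, so it need not be balanced.
2. The surgeon may carry out glenoid preparation, fixation and marker placement knowing which glenosphere will follow. A difference in migration could then partly reflect how the fixation was done. The same may apply to notching, which is central to the hypothesis. Later analysis cannot remove a bias introduced at that point.

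**Working it through.** **Order of events.**

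| Step | Position relative to allocation | Source |
|---|---|---|
| Bone-stock evaluation | Before | *Randomization* |
| Confirmation that a glenoid component can be inserted | Not stated | – |
| Glenoid fixation and glenoid markers | Not stated | – |
| Decision to convert to hemiarthroplasty | Not stated; listed in the section on violations, revision and drop-out | *Protocol violations, revision and drop-out* |
| Glenosphere | After, necessarily | *Surgical procedure* |

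The text fixes only the first and last rows. The wording suggests that allocation follows soon after the first, but sets no order for the three rows between.

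**The plan's sample sizes.** Inputs: for radiostereometry, SD 0.4 mm, difference 0.4 mm; for WOOS, SD 15, difference 10; for both, 5% significance (taken as two-sided), power 0.90, 20% drop-out.

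n per group = 2 × (1.960 + 1.282)² × (SD/difference)²

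- Radiostereometry: 2 × 10.51 × 1 = 21.0, rounded up to 22. 22/0.8 = 27.5, so 28 per arm and 56 in total, as stated.
- WOOS: 2 × 10.51 × 2.25 = 47.3, rounded up to 48. 48/0.8 = 60 per arm, 120 in total, against 122 stated. The difference is immaterial.

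**Effect of conversions.** The document gives no conversion rate, so c = 2–5% is an assumption, with 10% as an extreme. The unfavourable case adds conversions to a full 20% drop-out:

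evaluable per arm = (N/2) × (0.8 − c); power = Φ(√(n/2) × difference/SD − 1.960)

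| c | Converted of 56 | Evaluable per arm | Power, MTPM | Converted of 122 | Power, WOOS, converted excluded | Power, WOOS, converted kept |
|---|---|---|---|---|---|---|
| 0 | 0 | 22.4 | 0.917 | 0 | 0.909 | 0.909 |
| 2% | 1.1 | 21.8 | 0.911 | 2.4 | 0.902 | 0.897 |
| 5% | 2.8 | 21.0 | 0.900 | 6.1 | 0.890 | 0.879 |
| 10% | 5.6 | 19.6 | 0.879 | 12.2 | 0.869 | 0.842 |

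The last column assumes that converted patients show no difference between arms, so the difference shrinks to 10 × (1 − c) with 48.8 per arm. With the t distribution the MTPM powers are slightly lower: 0.905, 0.898, 0.885 and 0.862. If conversions fall within the 20% allowance, the first row applies.

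The possible bias from fixation with the arm known has no inputs in the document and is not calculated.

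**The case against.** The strongest reply is that the protocol does not say what a critic may read into it.

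- **A reader might infer that the surgeon places the glenoid fixation knowing the arm.** The article never orders randomisation against fixation. It makes this sequence possible, even likely, but does not state it.
- **A reader might infer that the exclusion for poor bone stock contradicts the conversion provision.** It does not. Failed insertion is wider than insufficient bone stock, and a screen followed by a contingency is coherent. The section on violations does not say that the converted patient was randomised. What stands is that the same patient could be counted either way.
- **A reader might infer that observed differences in notching would be due to placement.** The *Background* mentions several techniques against notching but goes on to name only lateral offset of the glenoid component, which is the intervention. It does not show that placement of the glenoid base drives notching or migration.
- **Technique is stated to be standardised.** The six surgeons are experienced and each must have done at least three lateralised procedures beforehand. This reduces the concern, but it is an intention; withholding the arm until the shared steps are finished would enforce it for those steps.
- **A common glenoid base is only implied.** Both implants are used according to the manufacturer's guidelines, which are not shown. If these require different preparation by implant, fixation with the arm known is part of the treatment compared, and allocation cannot move past that step. This objection stands and makes part of the fix conditional.
- **The power loss is small and the conversion rate assumed.** This also stands.

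The analysis of converted patients may be set out in a fuller document, so its absence alone would not be a finding. The timing of allocation, however, is a design choice that this article states.

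**Conclusion.** The point holds as a low-cost improvement in design. The article anchors allocation to a bone-stock evaluation and does not require that insertability be confirmed, or that glenoid fixation and markers be in place, before the surgeon is told the arm. Patients without a glenoid component can therefore already be randomised, and both fixation and the decision to convert can take place with the arm known.

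At an assumed 2–5% conversion rate, 1 to 3 of 56 patients would have no MTPM and 2 to 6 of 122 would have a hemiarthroplasty. Power for MTPM stays at about 0.90–0.91 on the normal approximation, so the documents do not support a claim that the trial becomes underpowered. The case rests on possible bias, whose size cannot be derived from the document. Nor can it be said that later allocation would remove all of it, since the surgeon must know the arm from the glenosphere onward.

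**What to change.** In *Randomization*, name the exact surgical step at which allocation is opened: the last step common to both arms, after the surgeon has confirmed that a reverse glenoid component can be used. If the sponsor confirms that both arms share the glenoid base and its preparation, place this after the base is fixed and the glenoid markers are in, immediately before the glenosphere is selected.

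Reconcile *Protocol violations, revision and drop-out* with the exclusion criteria and *Randomization*: a patient converted before allocation is logged as not randomised and does not count toward the 56 or the 122; a patient converted after allocation stays in the assigned arm, with the conversion recorded as a deviation. The conversion rule itself is a clinical matter and is not judged here.

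The cost is protocol wording. Randomisation already takes place in the operating room, with the primary investigator reading out the result. The choice between 4 mm and 8 mm rests on plain radiographs, so it does not appear to need earlier allocation. The downside is that the glenosphere is opened slightly later in the operation.

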### Sequence generation and allocation

The randomization done on the trial laptop is done in the Research Electronic Data Capture (REdCap), in which the computer generates the randomization sequence by block randomization, stratified for gender and age and equally randomized to both shoulders (1:1 allocation). The primary investigator reads the allocation from the trial laptop to inform the surgeon. An independent statistician prepares the randomization table before the study is initiated.

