## Methods and design

### Study design

This study is an investigator initiated, single-centre, 1:1 randomized controlled trial, which will compare the DELTA Xtend® Reverse Shoulder Lateralized Glenosphere Line Extension (intervention group) with the standard DELTA Xtend® Reverse Shoulder System (control group). The two implants are produced by Depuy Synthes (Raynham, MA, USA). The SPIRIT reporting guidelines [20] and checklist (Additional file 1: Appendix 1) were used.

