### Statistics

Prior to the analysis, the nature of the data is assessed. It is expected to analyse the changes between pre- and postoperative assessment with paired parametric statistics. The differences between the groups are expected to be analysed using parametric statistics (Student *t*-test). The radiostereometric analysis data is not expected to be normally distributed and will be analysed using non-parametric analysis of variance over time. The differences between these groups will be analysed with Mann-Whitney *U* test. Because of the nature of repeated measures in this study, it is expected to use a mixed effects model to analyse the overall results. Data on radiostereometric analysis and DXA will be analysed at the end of follow-up for the first 56 patients. No other interim data-analysis will be carried out.

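### Randomisation is stratified by gender and age but the named between-group tests do not use the strata; if the strata are prognostic, some precision is forgone, most clearly for MTPM

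*Protocol article*

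**What the plan says.** The trial is described under Study design as a "single-centre, 1:1 randomized controlled trial". Under Sequence generation and allocation, "the computer generates the randomization sequence by block randomization, stratified for gender and age". Block size and age cut-points are not given.

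The Statistics section names two between-group tests. In general, "The differences between the groups are expected to be analysed using parametric statistics", with the Student t-test as the method; this would cover WOOS, although WOOS is not named there. The radiostereometric data are treated as non-normal: "The differences between these groups will be analysed with Mann-Whitney *U* test". MTPM of the glenoid component at 2 years is the primary radiostereometric parameter. Neither test is described as stratified or adjusted.

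The same section adds that "it is expected to use a mixed effects model to analyse the overall results". The section on protocol violations, revision and drop-out treats that model as the final analysis when it deals with patients who leave the trial: "The patient in question will be included in the final mixed-effect model analysis". The model's fixed effects are not listed, so the article neither includes nor excludes gender and age.

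**The concern.** Stratified blocks make the arms nearly equal in gender and age. Differences between strata then contribute almost nothing to the true sampling variation of the treatment comparison. A plain t-test still counts that variation as noise, and a plain Mann-Whitney test does the same through the variance of its rank statistic. If the strata predict outcome, the nominal error is larger than the real one. The test then rejects less often than 5% under the null, and its interval is wider than the design requires.

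What is at stake is efficiency and calibration. The radiostereometric part is small, with 22 evaluable patients planned per arm, and the trial hopes to show that lateralisation does not increase migration, so a tighter migration estimate is worth having when it costs nothing.

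**Working it through.** **Inputs from the article.** WOOS: difference 10, SD 15, 5% significance, power 0.90, 48 per arm, 122 in total. MTPM: difference 0.4 mm, SD 0.4 mm, same significance and power, 22 per arm, 56 in total. Drop-out 20%. Sidedness is not stated; two-sided reproduces the figures.

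**Inputs assumed.** R², the share of outcome variance explained by the gender and age strata, is not in the document; I show 0 to 0.30. Balance within strata is taken as exact, and the stated SDs as total SDs, between-stratum variation included.

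**Step 1: reproduce the plan.** n per arm = 2(1.96 + 1.2816)² × (SD/difference)².
- WOOS: 2 × 10.51 × 2.25 = 47.3, so 48. For drop-out, 96/0.80 = 120 (stated 122).
- MTPM: 2 × 10.51 × 1 = 21.02, so 22. For drop-out, 44/0.80 = 55, or 28 per arm = 56 (stated 56).

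Both sizes rest on an unadjusted two-sample comparison and count on no gain from stratification. Noncentral-t power at these sizes is 89.8% (WOOS) and 90.0% (MTPM). The normal approximation used below gives 90.4% and 91.3%.

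**Step 2: effect of ignoring the strata.** Let SE = SD × √(2/n) and z = difference/SE.
- WOOS: SE = 15 × √(2/48) = 3.062, z = 3.266.
- MTPM: SE = 0.4 × √(2/22) = 0.1206, z = 3.317.

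Under balance the true standard error is SE × √(1 − R²). Hence:
- ratio of nominal to true standard error = 1/√(1 − R²)
- type I error of the unadjusted test = 2[1 − Φ(1.96/√(1 − R²))]
- unadjusted power = Φ((z − 1.96)/√(1 − R²))
- adjusted power = Φ(z/√(1 − R²) − 1.96)

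For WOOS at R² = 0.10, √0.90 = 0.9487. Unadjusted power is Φ(1.306/0.9487) = Φ(1.377) = 91.6%. Adjusted power is Φ(3.443 − 1.96) = Φ(1.483) = 93.1%.

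| R² | SE ratio | Type I error, unadjusted | WOOS power, unadjusted / adjusted | MTPM power, unadjusted / adjusted |
|---|---|---|---|---|
| 0 | 1.00 | 5.0% | 90.4% / 90.4% | 91.3% / 91.3% |
| 0.05 | 1.03 | 4.4% | 91.0% / 91.8% | 91.8% / 92.6% |
| 0.10 | 1.05 | 3.9% | 91.6% / 93.1% | 92.4% / 93.8% |
| 0.20 | 1.12 | 2.8% | 92.8% / 95.5% | 93.5% / 96.0% |
| 0.30 | 1.20 | 1.9% | 94.1% / 97.4% | 94.8% / 97.8% |

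The MTPM columns compare means on the normal approximation, so they are a guide to the rank tests rather than exact values for them.

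**Step 3: simulation check.** Four balanced strata, normal data, 6,000 replicates, R² = 0 / 0.10 / 0.20.
- WOOS t-test: power 90.1% / 91.0% / 92.0%, type I error 4.9% / 4.0% / 3.1%. Stratum-adjusted linear model: power 90.0% / 92.8% / 95.2%.
- Mann-Whitney in the MTPM setting (24 per arm, to divide evenly over four strata): power 90.8% / 91.4% / 92.7%, type I error 5.1% / 3.7% / 2.5%.

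The simulation agrees with the formulas and shows the same conservatism in the rank test. It used normal data, whereas the article expects MTPM to be non-normal.

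**The case against.** The strongest reply is that for WOOS nothing is wrong on the page. The t-test is only expected, a mixed model is also foreseen, and a list of its covariates commonly belongs in an analysis plan that is not shown. This largely stands. A reader might infer that the plan shuts gender and age out of the WOOS analysis, but the text does not say so; for WOOS the point is a request to make the adjustment explicit. The reply is weaker for MTPM. The Mann-Whitney wording is firm, the test in its plain form takes no covariates, and the article does not say whether the mixed model replaces it.

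Second, the loss depends on an R² that the article does not give. For WOOS the quantity of interest is change from the preoperative score, so what counts is how well gender and age predict change. At R² = 0 nothing is lost. This stands, and the conclusion is conditional for that reason.

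Third, balance will be approximate. The radiostereometric cohort is the first 56 patients, which may leave blocks incomplete, and 20% drop-out is allowed for. This stands too: the tabulated conservatism is nearer an upper bound for each R².

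Finally, a reader might infer that wider intervals are what endangers a claim of no increased migration. That claim depends first on how it is framed and tested, which is a separate matter that stratified analysis does not settle.

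**Conclusion.** The point holds as a minor one about efficiency and calibration. The named tests do not use the randomisation strata. If those strata are prognostic, the tests are conservative and less precise than an analysis that uses them. For R² from 0 to 0.20, adjustment would gain 0 to 2.7 percentage points of power for WOOS and 0 to about 2.5 for MTPM, and intervals would no longer be up to about 12% too wide. These figures assume near-exact balance within strata and the article's own SDs.

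It is tempting to read this as a trial that falls short of its planned power. The figures do not support that. The sample sizes never relied on stratification, and at the same R² the unadjusted power rises slightly above its value at R² = 0, because balance reduces the true variance. Setting 90% unadjusted against 93% adjusted would mix an R² of 0 with an R² of 0.10; the like-for-like WOOS comparison at 0.10 is 91.6% against 93.1%. Type I error stays at or below 5%, so validity is not in question.

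**What to change.** For MTPM, replace the plain Mann-Whitney test with a stratified rank test (van Elteren), or with a regression on ranks or on log MTPM that includes the randomisation strata. The radiostereometric cohort is small: 44 evaluable patients over, say, four strata (an assumption, as the age cut-points are not given) is 44/4 = 11 per stratum across both arms. A regression with gender and age group as two main effects avoids sparse cells and may be the safer choice.

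For WOOS, state that the primary between-group analysis is the mixed effects model with gender and age stratum, coded as in REDCap, as fixed effects, and that the unadjusted t-test is supportive.

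Fix both choices before the analysis of the first 56 patients, so that adjusted and unadjusted results cannot be chosen between afterwards. The cost is a sentence or two in the analysis text. No patients or measurements are added, the sample size stands, and the only statistical price is a few degrees of freedom.
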